### Sample size estimation

The sample size calculation is based on the study’s primary outcome: the mean difference in serum potassium levels within the prone-position cohort. Our preliminary data from 50 cases indicate that serum potassium concentration increases by a mean of 0.73 mmol/L (standard deviation [SD] 0.53) during the prone phase. While this large effect size would allow for statistical significance with a very small sample, we aimed to power the study to detect a more conservative, yet still clinically significant, difference of 0.5 mmol/L. Although the precise threshold for adverse cardiovascular effects associated with an acute potassium increase remains undefined, the relationship between serum potassium and cardiovascular events typically follows a U-shaped curve [5]. Recent evidence further suggests that the magnitude of potassium increase is a significant predictor of arrhythmias [6]. Therefore, in the clinical setting of esophagectomy, we considered a 0.5 mmol/L increase to be a clinically relevant safety margin. Assuming a paired t-test with a two-sided alpha of 0.05 and a power of 80%, a minimum of 34 patients in the prone-position cohort is required.

We plan to include all eligible patients from both institutions within the study period (January 2022 - December 2024), targeting a total sample size of approximately 150 cases. While the primary power calculation is met with 34 patients, this larger sample size will provide robust data for the secondary outcomes, including the multivariable regression analyses, ensuring greater precision and the ability to explore multiple predictor variables.

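### The minimum of 34 patients does not follow from 0.5 mmol/L and SD 0.53, which give 11; 34 is the answer for a standardised effect of 0.5

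*Protocol article*

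**What the plan says.** All the inputs stand in the protocol article under Methods, Sample size estimation.

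- **Pilot data.** The source is given as "Our preliminary data from 50 cases", in which potassium "increases by a mean of 0.73 mmol/L (standard deviation [SD] 0.53) during the prone phase". This is the only standard deviation in the article.
- **Target.** The authors set the pilot mean aside as too favourable and write that "we aimed to power the study to detect a more conservative, yet still clinically significant, difference of 0.5 mmol/L". The target is in raw units.
- **Test and result.** "Assuming a paired t-test with a two-sided alpha of 0.05 and a power of 80%, a minimum of 34 patients" are required.
- **Reuse of the figure.** The next paragraph plans about 150 cases and relies on the number again: "While the primary power calculation is met with 34 patients".

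No within-patient correlation, loss allowance, standardised effect size or second SD is given.

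**The concern.** A paired t-test sample size is fixed by the difference, the SD of the within-patient change, alpha and power. The article prints a value for each, and it prints the resulting number. A difference nearly as large as its SD needs only about a dozen pairs, so 34 is far too many for 80% power.

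Two things are at stake. First, the article says it is published before data access for transparency and pre-specification, yet the one sample size calculation for its primary outcome cannot be reproduced, and the figure is likely to pass into the results paper. Second, the text tells readers that the study is powered for a clinically meaningful 0.5 mmol/L, and the Discussion treats a statistically significant rise as strong evidence of clinical relevance in itself. On the article's own SD, significance can be expected for rises well below that margin.

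**Working it through.** **Inputs** (all from Sample size estimation): difference δ = 0.5 mmol/L; SD of the within-patient change σ = 0.53 mmol/L; two-sided α = 0.05; power 80%; paired t-test; stated minimum n = 34.

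**Formula.** With d = δ/σ, the test statistic follows a noncentral t distribution with n − 1 degrees of freedom and noncentrality d√n. Power is the probability that it falls beyond ±t(0.975, n − 1). The required n is the smallest with power of at least 0.80. The normal approximation, as a cross-check, is n ≈ [(1.960 + 0.842)/d]².

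**Step 1: what reproduces 34.** Take d = 0.5, that is, σ = 1.0 mmol/L for a 0.5 mmol/L difference.

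- Normal approximation: (2.802/0.5)² = 31.4.
- Exact power: 0.795 at n = 33 and 0.808 at n = 34.
- Required n = 34, an exact match.

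**Step 2: what the printed inputs give.** d = 0.5/0.53 = 0.943.

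- Normal approximation: (2.802 × 0.53/0.5)² = 8.8.
- Exact power: 0.757 at n = 10 and 0.805 at n = 11.
- Required n = 11. The stated figure is 34/11 = 3.1 times this.

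**Step 3: what 34 and 150 patients deliver at SD 0.53.**

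| n | Power for 0.5 mmol/L | Difference detectable with 80% power |
|---|---|---|
| 11 | 0.805 | about 0.5 mmol/L |
| 34 | 0.9996 | 0.26 mmol/L |
| 150 | above 0.9996 | 0.12 mmol/L |

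**Step 4: other readings of the inputs.**

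| Reading | Required n |
|---|---|
| One-sided test | 9 |
| 90%, 95% or 99% power | 14, 17 or 23 |
| α = 0.01, 80% power | 17 |
| Wilcoxon signed-rank efficiency adjustment | about 12 to 13 |
| Pilot mean 0.73 in place of 0.5 | 7 |
| 0.53 as the SD at each timepoint, zero correlation (SD of change 0.53 × √2 = 0.75) | 20 |
| Unpaired two-sample comparison | 18 to 19 per group (36 to 38 in total) |

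None gives 34. If 0.53 were the SD at each timepoint, an SD of change of 1.0 would need 2 × 0.53² × (1 − ρ) = 1.0, so ρ = 1 − 1/0.5618 = −0.78, an implausible negative correlation between two potassium values in the same patient. Inflating 11 to 34 for losses would need a loss of 1 − 11/34 = 68%, and no allowance is stated.

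**Step 5: could sampling error in the pilot SD justify 1.0?** Assuming normality, the 95% confidence interval for an SD of 0.53 from 50 cases is 0.44 to 0.66 mmol/L. At those limits the required n is 9 and 16. An SD of 1.0 lies far outside the interval.

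**The case against.** The strongest reply concedes the arithmetic and questions how much it matters. The stated minimum is larger than needed, not smaller. The study is retrospective and takes every eligible case in a fixed window, about 150, so nothing stops at 34 and no patient, test or data item depends on it. The authors also say openly that the pilot effect could be shown with very few patients and that the extra cases serve the secondary analyses. All of this stands. It limits the consequences, but it does not make the stated figure correct.

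A second reply is that the sentence containing 34 names no SD. The value 0.53 describes the pilot, so a different planning SD in a fuller document cannot be ruled out. That is fair as far as it goes. But 0.53 is the only SD offered and appears in the same paragraph as the basis of the calculation, and the SD that yields 34 is nearly double it and outside the pilot's own confidence interval. If such a value was used, the paragraph still needs correcting, because its readers will take 0.53 as the input.

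A third reply is that the mechanism is inferred. This also stands. The exact match at a standardised effect of 0.5 makes a raw difference entered as an effect size the likely explanation, but the article does not show it.

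**Conclusion.** The concern holds. With the article's difference, SD, test, alpha and power, the required number is 11, not 34, and 34 patients give 99.96% power for 0.5 mmol/L, not 80%. The figure 34 fits a standardised effect of 0.5, which at SD 0.53 is 0.5 × 0.53 = 0.265, or about 0.27 mmol/L.

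This rests on reading 0.53 as the SD of the within-patient change, which is how the sentence is worded. Reading it instead as the SD at each timepoint with zero correlation gives 20, still not 34. The defect lies in the correctness and reproducibility of the published justification. The primary test is amply powered, and no conclusion about the study's adequacy changes.

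**What to change.** Correct the sample size paragraph in one of these ways, according to what was actually done:

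1. State that for a difference of 0.5 mmol/L, SD of change 0.53 mmol/L, two-sided alpha 0.05 and 80% power, 11 patients are required, and change the later sentence that relies on 34.
2. Or keep 34 and state that it rests on a standardised effect of 0.5, about 0.27 mmol/L at SD 0.53, and drop the claim that it is the number for 0.5 mmol/L.
3. Or, if a planning SD near 1.0 mmol/L was intended, state it and justify it against the pilot value.

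Optionally, support the roughly 150 cases by precision: the expected 95% confidence interval half-width for the mean rise is t(0.975, 149) × 0.53/√150 = 1.976 × 0.0433 = 0.086 mmol/L. This would let readers judge the estimated rise against 0.5 mmol/L, which a significance test against zero does not do.

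The cost is a few sentences of text. No extra patients, data or analyses are needed.

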### Statistical analysis

The selection of the blood gas sample with the lowest pH during the intervention phase is a pre-specified criterion. This approach is not considered a selection bias but is rather a deliberate strategy to focus the analysis on the study’s primary research question: the physiological response, particularly in potassium homeostasis, to the most severe degree of acute acidosis encountered during the procedure.

All statistical analyses will be performed using R version 4.3.2 (R Foundation for Statistical Computing, Vienna, Austria). A p-value of less than 0.05 will be considered statistically significant.

#### Descriptive statistics.

Continuous variables will be presented as mean ± SD or median (interquartile range) as appropriate, while categorical variables will be presented as numbers (percentages).

#### Analysis for the primary outcome.

A paired t-test will be used to compare the mean serum potassium levels between the baseline and intraoperative timepoints.

#### Analyses for secondary outcomes.

**Analyses of Factors Associated with Potassium Increase:** For correlation analysis, Pearson or Spearman correlation will be used. For multivariable analysis of ΔK ⁺ , a linear regression model will be developed.**Sensitivity Analysis:** The primary outcome will be re-analyzed using a paired t-test on the subset of patients excluding those with severe metabolic acidosis.**Exploratory and Clinical Analyses:** For identifying risk factors for clinical hyperkalemia, a multivariable logistic regression model will be used. For subgroup analyses, the primary outcome will be compared between strata (e.g., using an independent t-test or ANOVA). Other exploratory analyses will be descriptive or use appropriate statistical tests as needed.

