## Methods

### Study design

This will be a retrospective, two-center observational study.

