**Analyses of Factors Associated with Potassium Increase:**
**Correlation Analysis:** To explore potential physiological drivers, correlations between the change in serum potassium (ΔK⁺) and changes in other variables will be assessed. These variables will include the change in PaCO₂ (ΔPaCO₂) and markers of metabolic stress, such as the change in lactate (ΔLac).**Multivariable Analysis of** Δ**K** ⁺ **:** A multivariable linear regression analysis will be performed to identify factors independently associated with the magnitude of the serum potassium increase (ΔK⁺). Candidate covariates for the multivariable model include the change in PaCO₂ (ΔPaCO₂), change in lactate (ΔLactate), baseline eGFR, fluid balance, norepinephrine dose, and the duration of the prone position. The final selection of independent variables will be determined based on clinical relevance, assessment of multicollinearity (e.g., variance inflation factor), and the sufficiency of outcome events to avoid overfitting.

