**Exploratory and Clinical Analyses:**
**Risk Factors for Clinical Hyperkalemia:** As an exploratory analysis, a multivariable logistic regression will be performed to identify risk factors for the development of clinically significant hyperkalemia (defined as serum potassium > 5.0 mmol/L).**Subgroup Analysis:** Subgroup analyses will be conducted based on key clinical factors, including **preoperative renal function (e.g., stratified by eGFR categories)** and bronchial blocker usage.**Assessment of Acid-Base Components:** Changes in other acid-base parameters (e.g., HCO₃ ⁻ , BE, anion gap) will be descriptively analyzed.

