Beyond this specific surgical procedure, our findings hold potential implications for the management of critically ill patients in the ICU, particularly those with respiratory failure. Patients with conditions such as Acute Respiratory Distress Syndrome (ARDS) often present with comorbid cardiac or renal dysfunction, making them exceptionally vulnerable to the life-threatening consequences of hyperkalemia. Our findings may suggest that hyperacute respiratory acidosis, in particular, warrants closer monitoring of electrolyte balance than previously appreciated. This perspective may also prompt a re-evaluation of permissive hypercapnia strategies. While permissive hypercapnia is employed to protect the lungs, its potential impact on electrolyte homeostasis is not fully understood.

Our exploratory multivariable analysis, by seeking to identify predictors for the magnitude of potassium increase, may help in identifying surrogate markers to define the safe limits of hypercapnia in critically ill patients.

This study has several methodological strengths. First and foremost, the use of a paired-design, where each patient serves as their own control, is a powerful approach to minimize the influence of inter-patient variability. Second, its two-center nature increases the generalizability of our findings. Furthermore, the collection of detailed, serial arterial blood gas data allows for a granular analysis of the acute physiological changes. Finally, our pre-specified plan to conduct a sensitivity analysis demonstrates a rigorous effort to isolate the effects attributable to respiratory changes, thereby strengthening the specificity of our conclusions.

Several limitations of this study should be acknowledged. First, its retrospective design leads to inherent variability in the timing of blood gas sampling and a lack of standardized protocols. Second, our study includes only patients in whom blood gas analysis was performed, potentially introducing selection bias. However, we believe this may have selectively enriched our sample with patients exhibiting more severe respiratory compromise, which aligns with our primary research question. Finally, distinguishing the precise contributions of respiratory and metabolic components to a mixed acid-base disorder is inherently challenging.

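### The only method stated for the exploratory bronchial blocker subgroup is an unadjusted comparison of users with non-users; an adjusted difference should be reported beside it

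*Protocol article*

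**What the plan says.** The protocol article describes the design thus: "This will be a retrospective, two-center observational study". Under Exploratory and Clinical Analyses it names two subgroup factors: preoperative renal function "and bronchial blocker usage".

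The method for subgroups is in Analyses for secondary outcomes: "the primary outcome will be compared between strata (e.g., using an independent t-test or ANOVA". No adjustment is mentioned.

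A separate linear model is planned for the potassium change: "A multivariable linear regression analysis will be performed to identify factors independently associated with the magnitude". Its candidate covariates are the changes in PaCO₂ and lactate, with "baseline eGFR, fluid balance, norepinephrine dose, and the duration of the prone position". Renal function is therefore both a subgroup factor and a candidate covariate. Blocker use is only a subgroup factor. The list is not closed: "The final selection of independent variables will be determined based on clinical relevance, assessment of multicollinearity" and on having enough data to avoid overfitting.

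The Data collection section records blocker use, surgical approach, BMI, history of respiratory dysfunction, and the presence, duration and pressure of CO₂ insufflation. It lists no hospital variable, although Participants names the two hospitals.

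**The concern.** A blocker is an intraoperative technique, not a fixed patient trait. In an observational study, those who received one may differ from those who did not in ways that also affect how much potassium rises. Approach, lung disease, body size and hospital practice are plausible examples. An unadjusted test assigns any such difference to the strata.

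The Discussion presents the paired design as a strength, with each patient as their own control. That holds for the primary outcome. Pairing removes stable differences between patients in potassium level. It does not balance blocker users and non-users on what drives the change.

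At stake is the interpretation of one exploratory contrast. The Discussion proposes partial lung collapse and CO₂ insufflation as part of the mechanism, so readers may take a blocker difference as evidence on that mechanism.

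**Working it through.** **Plan's own figure.** The article gives none for this contrast. Its minimum of 34 patients is for the primary paired test and plays no part here.

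**Inputs from Sample size estimation.** SD of the potassium change 0.53 mmol/L (50 preliminary cases); planned total about 150; two-sided alpha 0.05; power 80%.

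**Assumed inputs, because the article gives none.**
- Share of patients with a blocker: 20% or 50%.
- D, the difference between users and non-users in the proportion having one binary confounder: 0.2 to 0.6.
- G, the effect of that confounder on the potassium change: 0.2 to 0.5 mmol/L.
- No true blocker effect, and an SD of 0.53 in each group.

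**Step 1: precision of the raw comparison.** SE = SD × √(1/n₁ + 1/n₀).
- 50% use: 0.53 × √(1/75 + 1/75) = 0.087.
- 20% use: 0.53 × √(1/30 + 1/120) = 0.108.

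The difference detectable with 80% power is (1.96 + 0.84) × SE, about 0.24 mmol/L at 50% use and 0.30 mmol/L at 20% use.

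**Step 2: bias and its effect on the test.** Bias = D × G. The chance of p < 0.05 with no true effect is Φ(bias/SE − 1.96) + Φ(−bias/SE − 1.96).

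| D | G (mmol/L) | Bias (mmol/L) | P(p<0.05), 20% use | P(p<0.05), 50% use |
|---|---|---|---|---|
| 0.2 | 0.2 | 0.04 | 7% | 8% |
| 0.2 | 0.3 | 0.06 | 9% | 11% |
| 0.2 | 0.5 | 0.10 | 15% | 21% |
| 0.4 | 0.2 | 0.08 | 12% | 15% |
| 0.4 | 0.3 | 0.12 | 20% | 28% |
| 0.4 | 0.5 | 0.20 | 46% | 64% |
| 0.6 | 0.2 | 0.12 | 20% | 28% |
| 0.6 | 0.3 | 0.18 | 38% | 55% |
| 0.6 | 0.5 | 0.30 | 79% | 93% |

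The nominal rate is 5%. The mildest row is close to it. The strongest row has a bias as large as the difference the comparison can detect.

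**Step 3: price of adjustment.** For one binary confounder present in half the patients, R² between blocker use and the confounder is share × (1 − share) × D² / 0.25, and the adjusted SE is SE/√(1 − R²), holding the residual SD at 0.53.
- 50% use: R² is 0.04 to 0.36, so the SE rises from 0.087 to between 0.088 and 0.108.
- 20% use: R² is 0.026 to 0.23, so the SE rises from 0.108 to between 0.110 and 0.123.

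**The case against.** The contrast is exploratory. No aim, hypothesis or planned conclusion concerns blockers, and an unadjusted description of the potassium rise by stratum is legitimate if it is not read causally. A reader might infer that the study intends to claim a blocker effect; the article announces no such claim. This stands, and it keeps the point small.

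A reader might also infer that no adjusted analysis of blocker use will ever be done. The text does not establish that. The t-test and ANOVA are given as examples, the selection of linear-model covariates is open, and the logistic analysis ("a multivariable logistic regression will be performed to identify risk factors for the development of clinically significant hyperkalemia") lists no covariates. What can be said is that the only method stated for this contrast is unadjusted.

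The acknowledged limitation, "a lack of standardized protocols", might be taken as an admission about how blockers were chosen. It stands in a sentence on the timing of blood gas sampling and says nothing about blocker choice. The article nowhere says who chose a blocker or why. That use was not randomised follows from the design; the specific reasons for use are inference.

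Finally, the size of the bias rests wholly on assumed inputs, and the mildest case is near nominal. This also stands: the table shows what could happen, not what will.

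**Conclusion.** The point holds as a modest improvement to an exploratory analysis. For a non-randomised technique, the plan states an unadjusted comparison, although most of the variables needed to adjust it are already to be collected. A difference between strata could therefore reflect approach, lung disease, body size or hospital.

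The direction and size of the bias are unknown. With SD 0.53, 150 patients, and the assumed imbalance and confounder effects, it lies between 0.04 and 0.30 mmol/L, and the false-positive rate lies between 7% and 93%. Neither range is an estimate for this study. The documents do not support saying that the difference will be confounded to a material degree, or that it will be presented as causal. The primary outcome is unaffected.

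**What to change.** In Analyses for secondary outcomes, keep the raw difference by blocker use and add an adjusted difference with a 95% CI. Take it from a linear model of the potassium change on blocker use, surgical approach, BMI, history of respiratory dysfunction and hospital. Approach has three listed levels, so this is about 2 + 1 + 1 + 1 + 1 = 6 coefficients besides the intercept, or 150/6 = 25 patients per coefficient.

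Leave PaCO₂ change and insufflation pressure out of this model, because both may lie on the pathway from blocker use to potassium. For the same reason, adding blocker use to the candidate model already listed, which includes PaCO₂ change, would not give its overall difference.

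Cross-tabulate blocker use against approach and hospital first. If it nearly coincides with either, state that it is not separable and report the contrast descriptively only.

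The cost is one extra regression, a hospital code kept in the anonymised extract, and a somewhat wider interval: in the illustration, at most 0.108 against 0.087 in SE at 50% use, and 0.123 against 0.108 at 20% use.

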### Ethics and dissemination

This study protocol has been approved by the institutional review board of Aichi Medical University (Approval number: 2025−088) and the Aichi Cancer Center. As this is a retrospective study using anonymized data, the requirement for individual written informed consent was waived. An opt-out policy is in place for patient notification via institutional websites. All collected data will be anonymized. The findings will be disseminated through presentations at academic conferences and publication in a peer-reviewed journal. The study protocol has been registered with the University Hospital Medical Information Network Clinical Trials Registry (UMIN-CTR: UMIN000058829).

## Discussion

This study protocol was designed to address a critical clinical observation: a greater-than-expected elevation in serum potassium during prone-position esophagectomy. This finding stands in contrast to the conventional physiological understanding that respiratory acidosis—a common consequence of this procedure—causes minimal or no elevation in serum potassium, particularly when compared to metabolic acidosis [2–3]. Therefore, the primary objective of this study is first to confirm and quantify the mean increase in serum potassium between the supine (baseline) and prone-position phases. Given that acute respiratory acidosis is an almost inevitable event during this surgical phase, demonstrating a statistically significant potassium increase would, in itself, strongly suggest a clinically relevant phenomenon that challenges existing knowledge. However, we recognize that major surgery introduces multiple confounding variables that could influence potassium levels, such as metabolic stress. To address this complexity, our secondary analyses are designed to (1) assess the robustness of our primary finding via sensitivity analysis that controls for the effect of metabolic acidosis, and (2) explore the association between the potassium increase and various physiological drivers, including the severity of respiratory acidosis itself.

In particular, surgical techniques involving partial lung collapse and intrathoracic CO₂ insufflation may lead to rapid external CO₂ loading, resulting in acid-base changes distinct from those seen in endogenous respiratory acidosis. Multiple mechanisms, including H⁺/K⁺ exchange and altered ATPase activity, may contribute to this response. The body’s compensatory systems may not be able to fully respond to the acute rise in PaCO₂, potentially leading to more pronounced potassium fluctuations than typically expected.

The challenge of managing this surgically-induced state of respiratory compromise aligns with the central theme of our previous research: using specific, non-physiological models of difficult ventilation to elucidate fundamental truths about respiratory physiology. For instance, in our previous study, we focused on patients with severe airway stenosis undergoing airway stenting—another scenario involving extreme, surgically-created ventilatory compromise. In that setting, we challenged the conventional wisdom that muscle relaxants are contraindicated. Our previous prospective study demonstrated that controlled positive-pressure ventilation with muscle relaxants significantly reduced hypoxic events compared to maintaining spontaneous respiration [7]. That study highlighted how standard management approaches can fail in such unique circumstances. The current study extends this principle from the primary challenge of ‘ventilation failure’ to its secondary consequence, ‘electrolyte failure’. Both studies, therefore, underscore a common lesson: the body’s response under these non-physiological conditions can be far more significant than conventionally anticipated.

The potential findings of this study are expected to have direct implications for the perioperative management of patients undergoing prone-position esophagectomy. If a significant potassium increase is confirmed, it would strongly suggest that rigorous monitoring is essential. This implies that arterial blood gas analysis should be considered whenever significant hypercapnia is suspected, even in the absence of desaturation (low SpO₂). This is particularly crucial given the potential for a large arterial to end-tidal CO₂ gradient (PaCO₂-ETCO₂) in this setting, which can mask the true severity of respiratory acidosis [8]. Early detection of hyperkalemia would enable timely therapeutic interventions to mitigate the risk of adverse events. Furthermore, as this surgery involves direct manipulation in close proximity to the heart, it inherently carries a high risk of cardiac arrhythmias. The addition of acute hyperkalemia—a known pro-arrhythmic factor—could substantially amplify this risk, making its detection and management a critical safety priority.

Beyond this specific surgical procedure, our findings hold potential implications for the management of critically ill patients in the ICU, particularly those with respiratory failure. Patients with conditions such as Acute Respiratory Distress Syndrome (ARDS) often present with comorbid cardiac or renal dysfunction, making them exceptionally vulnerable to the life-threatening consequences of hyperkalemia. Our findings may suggest that hyperacute respiratory acidosis, in particular, warrants closer monitoring of electrolyte balance than previously appreciated. This perspective may also prompt a re-evaluation of permissive hypercapnia strategies. While permissive hypercapnia is employed to protect the lungs, its potential impact on electrolyte homeostasis is not fully understood.

Our exploratory multivariable analysis, by seeking to identify predictors for the magnitude of potassium increase, may help in identifying surrogate markers to define the safe limits of hypercapnia in critically ill patients.

This study has several methodological strengths. First and foremost, the use of a paired-design, where each patient serves as their own control, is a powerful approach to minimize the influence of inter-patient variability. Second, its two-center nature increases the generalizability of our findings. Furthermore, the collection of detailed, serial arterial blood gas data allows for a granular analysis of the acute physiological changes. Finally, our pre-specified plan to conduct a sensitivity analysis demonstrates a rigorous effort to isolate the effects attributable to respiratory changes, thereby strengthening the specificity of our conclusions.

Several limitations of this study should be acknowledged. First, its retrospective design leads to inherent variability in the timing of blood gas sampling and a lack of standardized protocols. Second, our study includes only patients in whom blood gas analysis was performed, potentially introducing selection bias. However, we believe this may have selectively enriched our sample with patients exhibiting more severe respiratory compromise, which aligns with our primary research question. Finally, distinguishing the precise contributions of respiratory and metabolic components to a mixed acid-base disorder is inherently challenging.

In conclusion, this study protocol describes a robust investigation into the clinically significant hyperkalemia associated with hyperacute respiratory acidosis, a phenomenon particularly relevant in modern thoracic surgery. While a randomized controlled trial comparing prone and lateral surgical approaches might have once been considered the ideal design, such a trial is likely no longer ethically or practically feasible given the established clinical benefits of the prone-position approach.

Therefore, a well-designed, multicenter observational study such as the present one represents the best available methodology to elucidate this important physiological question. The insights gained from this research have the potential to refine electrolyte management, prompt a re-evaluation of concepts like permissive hypercapnia, and ultimately improve the safety of patients both in the operating room and the intensive care unit.
